#### CBT+ intervention

The CBT+ intervention involves seven time points when materials are delivered across 6 weeks. The intervention will be delivered via: one face-to-face session of up to 75 min, to be conducted at the PMCC in the Chemotherapy Day Unit; one telephone call lasting approximately 20 min; seven emails (one per week that take approximately 15–20 min to read); and one brief telephone call (2–5 min) at the end of the intervention to ask about adverse events.

Intervention components delivered via email use the online software Mailchimp, which provides professional email templates and automates the timing of intervention delivery.

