##### Light therapy individualised protocol

The light therapy component will consist of daily use of light glasses for the 6-week duration of the intervention. Participants will receive a pair of Luminette® glasses with light intensity locked at 1500 lux and will be instructed to wear them for 20–30 min after awakening each morning. The specific timing of use will be established with each participant during the face-to-face session, and will be based on their individual sleep–wake timing and chronotype, accounting for early awakenings. A written light therapy manual covers the key components to be discussed in the face-to-face session.

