### Assessments and outcomes

Table 1 displays the measurements used in this study and the time points at which they will be administered. Screening interviews will be conducted in person during recruitment prior to randomisation. Baseline (week 0), mid-treatment (week 3), post-treatment (week 6), and 3-month follow-up (week 12) questionnaires with self-report measures will be completed online by emailing women a link to a survey on Qualtrics, or via telephone for women who prefer not to complete questionnaires online. Questionnaires completed via Qualtrics will be considered valid if they are completed within ±1 week of the planned time.

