### Statistical analyses

Primary analyses will be conducted on an intention-to-treat basis. Thus, results for all randomised women will be analysed in the group to which they were assigned, regardless of protocol violations. The only exception to this will occur if participants withhold or withdraw consent to use their data in the analysis. Statistical analyses will be conducted in R (data management, graphs, preliminary analyses) and MPlus using MplusAutomation [75]. As a preliminary step, data will be assessed for outliers and skew and, where appropriate, transformed or winsorised. Prior to primary analyses, we will produce a thorough descriptive profile of the sample, characterising both the dropout and missing data. There are no interim analyses planned. Statisticians will not be blinded.

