#### Baseline comparisons

Participant characteristics at baseline will be presented by treatment group, and statistical tests will be conducted to verify that randomisation was successful. Discrete variables will be summarised by frequencies and percentages, and baseline group differences tested using chi-square tests. Continuous variables will be summarised using mean (standard deviation) or median (interquartile range) and baseline group differences, tested using independent *t* tests or Wilcoxon signed-rank tests for variables that evidence non-normal distributions. If there are significant differences in any participant characteristics at baseline, the variable(s) will be included as covariates in the final analyses.

#### Aim 1

Aim 1 is to test the efficacy of CBT+ compared to TAU+ for improving symptoms of sleep disturbance. Aim 1 will be tested using LGMs. LGMs will be estimated with an intercept and two linear slopes, representing a piecewise model. Slope 1 will have loadings constrained to 0, 0.5, 1.0 and 1.0 for weeks 0, 3, 6 and 12, respectively, capturing the linear change from baseline (week 0) to post-intervention (week 6). Slope 2 will have loadings constrained to 0, 0, 0 and 1.0 for weeks 0, 3, 6 and 12, respectively, allowing a different slope from post-intervention (week 6) to follow-up (week 12) compared to from baseline (week 0) to post-intervention (week 6). The means and variances of the intercept and slope factors will be freely estimated (corresponding to random effects in linear mixed models) and the intercept and slope covariances will be estimated. The residual variance will be constrained to equality across time and residuals assumed uncorrelated, corresponding to an independent, homogenous residual structure. Intercepts of indicators will be constrained to 0 to allow estimation of the latent random intercept mean.

There are two stratification factors: screening ISI (≤7, ≥8) and cancer stage (≤2, ≥3). These factors will be crossed, creating four groups: early-stage, low ISI; advanced-stage, low ISI; early-stage, high ISI; and advanced-stage, high ISI. Dummy codes will be created for each strata, with early-stage, low ISI treated as the reference group. These dummy codes will be included as covariates to adjust for their effect on the random intercept following recommendations that stratification factors be adjusted for in analyses of randomised controlled trials [76, 77].

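### The ±1 week validity rule lets a post-treatment ISI count up to a week before the 6-week course is completed, and declares later Qualtrics answers not valid, in tension with the intention-to-treat statement

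*Protocol article*

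**What the plan says.** Under Assessments and outcomes, the protocol article schedules "Baseline (week 0), mid-treatment (week 3), post-treatment (week 6), and 3-month follow-up (week 12) questionnaires", completed through an emailed survey link "or via telephone for women who prefer not to complete questionnaires online". It then sets the validity rule: "Questionnaires completed via Qualtrics will be considered valid if they are completed within ±1 week of the planned time".

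The treatment runs for the whole period up to the nominal week-6 visit. The CBT+ intervention section says "The CBT+ intervention involves seven time points when materials are delivered across 6 weeks", including "seven emails (one per week that take approximately 15–20 min to read". The light therapy section specifies "daily use of light glasses for the 6-week duration of the intervention".

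The ISI is one of two primary outcomes, defined as change from baseline to post-intervention. The Aim 1 analysis fixes the time coding: "Slope 1 will have loadings constrained to 0, 0.5, 1.0 and 1.0 for weeks 0, 3, 6 and 12, respectively". The treatment effect on slope 1 is the primary result. The opening of Statistical analyses promises that "results for all randomised women will be analysed in the group to which they were assigned, regardless of protocol violations".

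**The concern.** The window is symmetric around a time point that marks the end of treatment. Its early half therefore admits scores taken before the course is completed. Because the loadings are tied to nominal weeks, such a score enters at 1.0, as if the full course had been received. In CBT+ this can pull the estimated slope 1 effect on the ISI towards zero.

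Its late half has a different problem. A Qualtrics answer after day 49 has been observed but is called not valid. If that means it is left out, the trial discards primary outcome data that it holds. It would do so for a reason (lateness) that could be related to illness during chemotherapy or to arm, since the arms have different contact schedules. The article shows neither relation, but its commitment to analyse results regardless of protocol violations is meant to avoid exactly this kind of exclusion.

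**Working it through.** **Inputs.** Planned times are weeks 0, 3, 6 and 12, with a window of ±7 days (Assessments and outcomes). There are seven weekly emails and 6 weeks of light therapy (intervention sections). Planned d = 0.70, 70 women in total, α = 0.05 (Sample size and power). 101 women were randomised (Trial status). Assumptions not in the article: a two-sided test, and 35 women per arm out of 70.

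**1. The plan's own figure.** A two-sample t test with 35 per arm, d = 0.70 and two-sided α = 0.05 has 82.3% power. The stated figure of more than 80% is reproduced and is not in question.

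**2. The windows in days.** Week 6 is day 42, so 42 − 7 = 35 and 42 + 7 = 49. A Qualtrics answer is valid on days 35 to 49.

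**3. Treatment received by day 35.** Light therapy: 35 of 42 days. Emails: if the first goes out on day 0, the seven fall on days 0, 7, 14, 21, 28, 35 and 42, so six are sent by day 35. If the first goes out on day 7, five are sent. The course is largely delivered by then, but not completed.

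**4. Attenuation of the ISI effect.** Let the effect build linearly to day 42, as slope 1 itself assumes, and stay flat after that: d(t) = 0.70 × min(t, 42)/42. At day 35, d = 0.70 × 35/42 = 0.583, a loss of 1/6. If a share p answers on day 35 and the rest on or after day 42, the average is d = 0.70 × (1 − p/6). The article does not give p, so a range is shown:

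| Share p answering on day 35 | d | Power, 70 women | Power, 101 women (50 v 51) |
|---|---|---|---|
| 0 | 0.700 | 82.3% | 93.6% |
| 10% | 0.688 | 81.0% | 92.9% |
| 25% | 0.671 | 79.0% | 91.6% |
| 50% | 0.642 | 75.4% | 89.1% |
| 100% (bound) | 0.583 | 67.2% | 82.7% |

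Answers spread evenly over days 35 to 49 would be early in half of cases, by 3.5 days on average: d = 0.70 × (1 − 0.5 × 3.5/42) = 0.671, power 79.0% with 70 women. The last column assumes that all 101 women contribute a week-6 ISI, so it is a best case.

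**5. Late scores treated as missing.** With d held at 0.70 and a fraction of week-6 scores lost, the t test power is:

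| Week-6 scores lost | 70 women | 101 women |
|---|---|---|
| 5% | 80.3% | 92.4% |
| 10% | 78.1% | 91.0% |
| 20% | 73.0% | 87.4% |

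The growth model also uses each woman's other time points, so the t test figures are only a guide to the cost.

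**6. Which outcomes are touched.** Diary sleep efficiency comes from daily paper diaries, not Qualtrics, so the rule does not reach it.

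**The case against.** A ±1 week tolerance is ordinary. The article does not say when the survey link is emailed, and if it goes out at week 6 few or no answers will be early. How out-of-window scores are handled is often left to a statistical analysis plan. With 101 women randomised there is room to spare on power. All of this stands as a limit on size: the harm is possible and bounded, not demonstrated. It does not remove the point, because the article itself fixes both the validity rule and the nominal loadings, and a larger sample does not undo attenuation of the estimate.

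Four stronger readings are tempting and not supported:

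- **The intention-to-treat set is broken.** It is not shown to be. A woman with an out-of-window questionnaire remains randomised, analysed as assigned, and in the growth model through her other time points. She would lose one observation, and the article does not say outright that even this is excluded. What exists is a tension between two statements.
- **The primary endpoint is diluted.** This depends on an unstated share of early answers and concerns the ISI only.
- **Baseline may also be taken a week into treatment**, leaving 4/6 of the effect (d = 0.70 × 4/6 = 0.47, power 49%). This needs every woman to be at both extremes. Randomisation is stratified on baseline ISI, so an ISI score must exist before allocation. Aim 1 calls the stratifier screening ISI, so a separate later baseline cannot be wholly excluded, but this is a corner case and not an estimate.
- **Telephone answers have no window at all.** The text does word the rule for Qualtrics only, but the full protocol may cover telephone. This is minor.

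**Conclusion.** The point holds in bounded form. As written, a post-treatment ISI is accepted from day 35, up to one week before the course is completed, and is scored as full-course. An observed Qualtrics answer after day 49 is declared not valid, against the spirit of the intention-to-treat statement.

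Under linear accrual the ISI effect can be attenuated by at most 1/6, and by about 2% to 8% if 10% to 50% of women answer on day 35. The corresponding power loss with 70 women is about 1 to 7 percentage points. With 101 randomised it is smaller, but the proportional attenuation is the same. These figures rest on an assumed share of early answers and an assumed shape of effect, neither of which the article gives. The stated power calculation is not in error. The change is worth making because it is cheap and removes both the mistiming and the avoidable missing data.

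**What to change.** In the primary intention-to-treat ISI analysis, keep every completed questionnaire, whether by Qualtrics or telephone, and model time from its actual completion date relative to the start of the intervention period, defined in the same way in both arms. In the piecewise model this means individually varying times. With t in days from the start, the slope 1 loading is min(t, 42)/42 and the slope 2 loading is max(t − 42, 0)/42, both set to 0 for a baseline completed before the start. At days 0, 21, 42 and 84 these return the planned loadings of 0, 0.5, 1, 1 and 0, 0, 0, 1.

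Restrict to answers within ±1 week only as a sensitivity analysis, and say so. Report the distribution of week-6 completion times by arm, so that a reader can see how many scores were early or late and whether this differs between arms.

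For any woman not yet assessed, do not open the post-treatment questionnaire before the end of week 6. This will help few women, since recruitment closed in October 2019; the analysis change is what matters.

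The cost is a revised analysis paragraph and slightly more model set-up. It needs completion dates, which an online survey would normally record and which must be available for telephone interviews too.

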**Table 1 Tab1:**
[figure not shown]
Assessment measures used in the CBT+ study

X indicates measure administered at that time point; N items indicates the number of items in each scale; a continuous line indicates measured/undertaken continuously

*CBT+* combined cognitive behavioural therapy and bright light therapy, *PROMIS* Patient-Reported Outcomes Measurement Information System, *TAU+* treatment as usual plus relaxation audios

During the intervention phase, sleep will be assessed continuously via daily sleep diaries and actigraphy. Sleep diaries will be provided to all women in a paper and pencil format only. The actigraphy watch (ActiGraph wGT3X-BT) is of similar size to a regular wristwatch and will be worn by women continuously during the 6-week intervention. For women in the CBT+ group, the sleep diary also will assess daily light therapy adherence. Prior to commencing the intervention, women will be supplied with six diaries, one for each week of the intervention, and six pre-paid addressed envelopes so that at the end of each week women can post that week’s diary to the research team. Outcome assessment is not blinded as all outcomes (except for sleep based on actigraphy) are patient-reported outcomes.

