## Method

### Study design

This is a randomised, two-group, parallel, non-blinded, controlled, single-centre, superiority trial. One group will receive combined CBT plus BLT (CBT+). The other group will receive treatment as usual enhanced with a relaxation audio programme serving as an active control (TAU+). All participants will be involved in the trial for the 6-week duration. Measures will be taken at baseline, at the mid-point of the intervention (3 weeks) and post-treatment (6 weeks). A follow-up assessment will occur at 3 months to evaluate any sustained effects of the intervention on primary and secondary outcomes. This trial and protocol adhere to SPIRIT [48] and TIDieR [49] recommendations.

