#### Secondary outcome measures

Secondary outcomes will include additional dimensions of sleep behaviours assessed via self-reported sleep diaries and actigraphy, and symptoms of fatigue, depression and anxiety. Sleep-onset latency, wake after sleep onset and total sleep time will be derived from the sleep diaries and the ActiGraph. The ActiGraph wGT3X-BT records continuous activity information using a three-axis accelerometer along with ambient light. Using the activity data, the wGT3X-BT provides estimates for sleep timing (bed time and rise time), sleep duration (time in bed and total sleep time), and sleep quality (sleep efficiency, sleep-onset latency, wake after sleep onset). Actigraphy data scoring will follow standard protocol, integrating estimates from the automated scoring algorithm along with ambient light, and sleep diary reports of bed and rise time. Actigraphy sleep assessments are time and date stamped so that they can be matched with the self-report sleep diary measures. In sleep studies it is common to evaluate the impact of interventions on multiple behavioural dimensions of sleep as not all dimensions may change. Furthermore, it is helpful to supplement self-reported sleep with an objective measure (actigraphy). Evidence suggests that, often, there is only modest agreement between sleep diary and actigraphy, suggesting that these two measures capture unique information and are not redundant [58].

The Patient-Reported Outcomes Measurement Information System (PROMIS) scales will be used to assess other secondary outcomes including sleep-related impairment and sleep disturbance [59], fatigue [60], and mental health measures of depression and anxiety [61].

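### The reason given for unblinded outcome assessment does not cover actigraphy, whose scoring draws on diaries that show the arm in CBT+

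*Protocol article*

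**What the plan says.** The article is open about the lack of blinding. Study design describes a "randomised, two-group, parallel, non-blinded, controlled, single-centre, superiority trial". Statistical analyses adds "Statisticians will not be blinded". The reason is given once, in the text below Table 1: "Outcome assessment is not blinded as all outcomes", with a bracketed exception for actigraphic sleep, are reported by the patient.

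Secondary outcome measures says that actigraphy scoring follows standard protocol, "integrating estimates from the automated scoring algorithm along with ambient light, and sleep diary reports of bed and rise time". The same section presents actigraphy as an objective measure that supplements self-report.

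On the diaries, the text below Table 1 says "Sleep diaries will be provided to all women in a paper and pencil format only", to be posted to the research team week by week. It also says "For women in the CBT+ group, the sleep diary also will assess daily light therapy adherence".

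Both primary outcomes, the ISI and diary sleep efficiency, are self-reported (Primary outcome measures). Actigraphy is secondary.

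**The concern.** Patient report is a sound reason for not masking an assessor when the assessor is the unblinded woman herself. It is no reason for actigraphy, where someone or something other than the woman turns the recording into sleep variables. The sentence that gives the reason makes that exception and then draws no consequence from it. If the bracket was meant to convey that actigraphy is scored masked, the sentence does not say so.

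The route by which the arm could become known is visible in the text. Diary times feed into the scoring, and a CBT+ diary can be told from a TAU+ diary by its light-therapy items. Where algorithm, light and diary disagree about when the rest period began or ended, someone who knows the arm may resolve the disagreement in its favour. That interval is the denominator of sleep efficiency and also bears on sleep-onset latency and wake after sleep onset. What is at stake is how much weight an actigraphy result can carry beside two primary outcomes rated by women who know their treatment.

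**Working it through.** The point rests on the text, so the statements are set side by side first. The arithmetic after that gives scale only.

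**1. Does the stated reason cover actigraphy?** Reason: outcomes are patient-reported. Exception in the same sentence: sleep based on actigraphy. The reason does not cover it, and the article describes no masking of its scoring.

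**2. Does diary information enter the scored outcome?** Yes. Three sources are named: the algorithm, ambient light, and diary bed and rise times.

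**3. Does the diary disclose the arm?** An unredacted one does, because only the CBT+ version has light-therapy adherence items.

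**4. What is not stated?** Who scores, whether any step is done by hand, and whether the scorer sees the whole diary or only the two times.

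**5. The plan's own figure.** Sample size and power gives 70 women, d = 0.70, α = 0.05 and power above 80%. Assume 35 per arm and a two-sided test. The noncentrality is 0.70 × √(35 × 35/70) = 0.70 × 4.183 = 2.93. The normal approximation gives Φ(2.93 − 1.96) = 83.4%, and the exact noncentral t gives 82.3%. The stated figure reproduces, and masking the scorer changes nothing in it.

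**6. Scale of one boundary decision.** Assumed values, not in the documents: 7.5 h in bed and 6.4 h asleep.
- Starting efficiency: 6.4/7.5 = 85.3%.
- Remove 15 minutes from the interval, all of it wake: 6.4/7.25 = 88.3%.
- Remove 15 minutes containing sleep in the average proportion: (6.4 − 0.25 × 0.853)/7.25 = 85.3%, no change.

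So a 15-minute trim moves efficiency by between 0 and 3 percentage points over these two cases. The larger figure would bias the arm comparison by that much only if the same choice were made every night and in one arm only. Boundary error unrelated to arm adds noise, not bias.

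**7. Scale for the test.** Suppose there is no true effect and unmasked scoring shifts one arm's mean by b SD. The two-sided 5% t test then has noncentrality b × √(n₁n₂/(n₁ + n₂)) on n₁ + n₂ − 2 degrees of freedom. Sizes: 35 per arm (the 70 completers), and 50 and 51 (the 101 randomised, assuming a near-even split and usable actigraphy from all).

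| Assumed b | Rejections, 35 and 35 | Rejections, 50 and 51 |
|---|---|---|
| 0 | 5.0% | 5.0% |
| 0.1 | 7.0% | 7.9% |
| 0.2 | 13.1% | 16.9% |
| 0.3 | 23.6% | about 32% |

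No value of b can be derived from the documents. The table shows only what a given shift would do.

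**The case against.** The strongest reply is that the scoring may leave little or nothing to judgement. The article refers to a standard protocol and an automated algorithm, and names only bed and rise times as diary inputs. Integration could be rule-based, and the light-therapy items might never reach the scorer. A journal article may leave such procedure to the full protocol, which this one says will be posted. The lack of blinding is declared, not hidden, and actigraphy is secondary.

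Much of this stands. A reader might infer that scoring is manual, but the article does not say so. A reader might also conclude that actigraphy carries the same expectation bias as the primary outcomes and so cannot support them independently. That goes too far: the sleep and wake estimates start from accelerometer data and an algorithm, and a scorer could influence only the part open to discretion. The woman's own bed and rise times enter the scoring in any case, so masking the scorer would not remove her expectations from that input.

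The reply does not repair the stated reason. The article makes a positive statement about outcome assessment, and the ground it gives excludes actigraphy. That is a design choice expressed on the page, not a detail left elsewhere.

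**Conclusion.** The point holds as a minor improvement. The justification for unblinded assessment does not apply to actigraphy, and the scoring uses a diary whose CBT+ version reveals the arm if passed on unredacted. This leaves the objective supplement open to an avoidable scorer bias wherever judgement enters. Its value is weakened, not lost.

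The size is unknown. The shift from 85% to 88% is a worst case under assumed sleep times, and the inflated error rates depend on assumed shifts. Neither is an estimate for this trial. The ISI, diary sleep efficiency, the sample size and the primary tests are unaffected.

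It might also be inferred that masking could be arranged with no extra staff. The documents do not support that. They give no staffing figures, and Ethics approval and safety monitoring calls the trial minimally funded. The one staff member placed outside recruitment and delivery generated the randomisation scheme, and the same initials appear for a supervisor of the therapist.

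**What to change.** Amend the sentence below Table 1 so that the patient-report reason is confined to the patient-reported outcomes, and add to Secondary outcome measures that:
- actigraphy is scored on files identified by study number only, with arm removed;
- the scorer receives only transcribed bed and rise times, without the light-therapy items;
- scoring is locked before arm codes are merged;
- where the existing team allows, the scorer is someone who did not deliver that woman's session.

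If any scoring has already been done otherwise, or masking is not possible, the article should say so and the results should be reported with that limit.

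The cost is some file preparation. Study numbers are already in use (Data storage and confidentiality), and diary times presumably have to be entered anyway to compute diary sleep efficiency. No participant procedure or sample size changes. Trial status expects follow-up to end by January 2020 and Data Availability reports no datasets yet generated or analysed, so the change may still be in time. The protection depends mainly on what is stripped from the files, since the documents do not show that a scorer unaware of allocation is available.
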